### Rescue therapy and concomitant medications

3.7

If a participant experiences unbearable pain at the screening visit, he/she may be allowed to take acetaminophen. If the participant takes any rescue medication, the date and dose of administration will be recorded in the study participant's log. The dose of rescue medications should not exceed 4000 mg/day and should not be taken within 8 h prior to the participant's log entry for every morning. Moreover, medication is permitted in the following cases:

1.continuous low-dose aspirin use that was prescribed for non-analgesic purposes at a fixed dose 1 month before the run-in period (≤375 mg/day), hypoglycemic agents, and hypertension drugs (however, the dose taken or the regimen at the start of the study of the low-dose aspirin does not change throughout the clinical trial);2.medications that were being taken by participants at the time of screening and would not affect the results of this clinical trial;3.the administration of the drugs used for the transient treatment of other disorders will be determined at the discretion of the principal investigator (or sub-investigator or attending physician).

If concomitant medication is administered during the trial period, the name of the drug, the daily dose, and the duration of administration should be noted on the case report form.

### Study outcomes

3.8

#### Primary outcome

3.8.1

The primary outcome in this study measures the changes in the Functional Assessment of Cancer Therapy/Gynecologic Oncology Group Neurotoxicity (FACT/GOG-Ntx) subscale (version 4.0, Korean) in comparison with the baseline, in which scores from 11 questions, each consisting of 0 to 4 points will be evaluated. A higher score indicates a more severe degree of peripheral neuropathy.^[20,21]^ The FACT/GOG-NTX questionnaire is to be self-administered by the participants.

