### Study design

3.2

This study is designed as an open-label, parallel, assessor-blinded randomized controlled trial. This study will be conducted at the Catholic Kwandong University International St. Mary's Hospital, Incheon, South Korea. The diagrammatic representation of this study is presented in Figure 1. The patients will receive a full explanation of the details of the trial from investigators. Through this procedure, if they agree to participate in the trial, a signed consent form will be obtained.

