#### Inclusion criteria

3.5.1

The inclusion criteria as follows:

1.adult men and women aged 18 to 85 years;2.patients with colorectal cancer with oxaliplatin-induced peripheral neuropathy or patients with breast cancer patients with taxane-induced with peripheral neuropathy (provided that the patients have had peripheral neuropathy for 1 month or longer after the chemotherapy before the time of screening and have peripheral grade 2 or higher sensory/motor neuropathy, based on the Common Terminology Criteria for Adverse Events (CTCAE) V5.0 at the time of screening);3.those who do not have significant restrictions on their behavior and life, corresponding to Eastern Cooperative Oncology Group (ECOG) 0–2;4.patients who can read the symptom questionnaire, comprehend it, and answer accordingly;5.patients who have given their consent for the clinical protocol and follow-up and in the Institutional Review Board (IRB)-approved document.

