The pregabalin used in this study is not a clinical investigational product and does not require allocation concealment, since it is administered to all groups. Moreover, it is impossible to blind the investigator and the participant in each group due to the nature of the study intervention, which is based on the contact between the patient and the medical staff. Instead, the investigator maintains blinding to prevent bias in evaluating the participant. If the clinical trial is completed, all clinical report forms (CRFs) are collected, the database process is terminated, and unblinding will be performed, if required for statistical analysis. Moreover, if it is deemed necessary to confirm the subject group due to an emergency situation during the clinical trial, the randomization code will be disclosed only to the participant, according to the principal investigator's discretion. If it is not possible to consult with the principal investigator and the situation is urgent, the randomization code of the subject will be disclosed after consultation with the randomization code officer. If unblinding is performed, the documentation of the reason for the unblinding will be retained and the participant with the disclosed randomization code will not be able to continue the trial.

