#### Secondary outcome

3.8.2

Secondary outcome assessment measures the change and rate of change in the Quality of Life Questionnaire-CIPN 20-Item Scale (EORTC QLQ-CIPN 20) and Quality of Life questionnaire (EORTC QLQ-C30, version 3.0) developed by the European Organisation for Research and Treatment of Cancer in comparison to the baseline.^[22–24]^ EORTC QLQ-CIPN 20 consists of 20 questions, with 9 sensory nerve-related questions, 8 motor neuron-related questions, and 3 autonomic nerve-related questions. A higher score indicates a more severe degree of peripheral neuropathy.^[22]^ EORTC QLQ-C30 is a tool for measuring health-related quality of life and consists of 2 items of the overall functional state, 15 items of function, and 13 items of symptoms. A lower overall score indicates a better quality of life.^[25]^

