#### Exploratory efficacy

3.8.3

Exploratory efficacy evaluation is based on the chemotherapy completion rate and NCS. The chemotherapy completion rate is used for patients enrolled in clinical studies where chemotherapy is in progress and is calculated as follows: chemotherapy completion rate = number of chemotherapy sessions completed after research project/chemotherapy sessions planned in the future∗100. The time point of investigating the chemotherapy completion rate is when all scheduled chemotherapy schedules are completed. NCS is performed as a statistical selective test and is conducted in 1 to 2 of 10 patients. The visit-window of the NCS that should be performed during the baseline visit will be ± 4 days.

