### Statistical analysis

3.9

All statistical analyses will be conducted by a blinded professional statistician. All participants who provided written consent and were assigned a screening number for the study are included in the screening set, and patients randomized to the treatment group are included in the randomized set. Intention-to-treat (ITT) analysis will be performed in patients who have received at least one pregabalin trial or at least one session of acupuncture or CMT. Per-Protocol Set (PPS) analysis will be performed in patients who meet the inclusion/exclusion criteria, have no significant conditions affecting the efficacy assessment, show > 80% treatment compliance, and have performed at least one evaluation after the baseline evaluation.

The statistical analysis for the efficacy evaluation, based on ITT analysis and PPS analysis are conducted in parallel. All statistical tests will be performed as two-sided tests with a significance level of 5%, and two-sided 95% confidence intervals. Primary outcome assessments are performed with ANOVA analysis to test the differences between the groups for changes in FACT/GOG-NTX at the end of week 5, compared to baseline. If the differences between groups are significant, the Tukey method will be used. For secondary outcome evaluation, continuous variables are analyzed with ANOVA analysis or Kruskal–Wallis test, and categorical variables are analyzed with Pearson's chi-squares test or Fisher's exact test. The Exploratory Efficacy assessment will summarize the descriptive statistics on the chemotherapy completion rate, followed by the appropriate statistical analysis.

For the occurrence of adverse events, the number of cases, number of participants, severity, and causal relationship with the investigational drug can be statistically analyzed by group, and nonparametric methods can be applied as needed. The results of vital signs, physical examination, electrocardiograms, and laboratory tests will be reviewed in a comprehensive manner, and statistical analysis will be conducted as necessary for the test items deemed clinically significant by the investigators. Depending on the nature of the data, continuous data will be summarized by observed values, mean, standard deviation, median, minimum, and maximum for each visit, and categorical variables will be summarized by frequency and percentage.

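### Assessor blinding does not protect the main efficacy comparison, because unblinded participants rate the primary outcome themselves, and section 3.6 does not say coherently who is blinded

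*Protocol article*

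**What the plan says.** The title and abstract carry the assessor-blinded label, and section 3.2 repeats it: "This study is designed as an open-label, parallel, assessor-blinded randomized controlled trial".

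Section 3.6 explains the blinding in two consecutive sentences. The first says that "it is impossible to blind the investigator and the participant in each group due to the nature of the study intervention". The second reads: "Instead, the investigator maintains blinding to prevent bias in evaluating the participant".

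On who rates the outcomes:

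- **Primary (3.8.1).** Change from baseline in the FACT/GOG-Ntx subscale. "The FACT/GOG-NTX questionnaire is to be self-administered by the participants".
- **Secondary (3.8.2).** Change in two EORTC questionnaires, QLQ-CIPN20 and QLQ-C30. The section does not say who completes them. Inclusion criterion 4 in section 3.5.1 requires "patients who can read the symptom questionnaire, comprehend it, and answer accordingly".
- **Exploratory (3.8.3).** Chemotherapy completion rate, and nerve conduction studies: "NCS is performed as a statistical selective test and is conducted in 1 to 2 of 10 patients".
- **Safety (3.8.4).** Physical examination, vital signs, electrocardiogram, adverse reactions, laboratory tests and neurological tests.

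Section 3.9 states that the statistician is blinded.

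**The concern.** Section 3.6 presents a blinded evaluator as what stands in for the participant blinding that cannot be had. That works only if the evaluator produces the measurement being compared. For the primary outcome the patient produces it, and the patient knows the arm.

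The arms also differ in contact and in what a patient may expect from them. There is no sham or attention control, and pregabalin alone is compared with pregabalin plus a course of hands-on sessions. Any effect of expectation on how a patient fills in the form passes directly into the primary contrast. A reader who meets the assessor-blinded label in the title may credit that contrast with a protection it lacks, and a positive result may be reported in the same terms.

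The wording of section 3.6 adds a second problem. Taken literally, the investigator both cannot be blinded and is blinded, so it is unclear whose blinding the label refers to.

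**Working it through.** No figure in the plan is at stake, so the check is mainly a reading of who rates what.

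**Step 1: rater and blinding, outcome by outcome.**

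| Measure | Who rates it | Does that rater know the arm? |
|---|---|---|
| FACT/GOG-Ntx (primary) | Participant, stated in 3.8.1 | Yes, by 3.6 |
| QLQ-CIPN20, QLQ-C30 (secondary) | Participant, inferred from the questionnaire format and inclusion criterion 4 | Yes, if the inference is right |
| Nerve conduction (exploratory) | Staff | Not stated |
| Chemotherapy completion (exploratory) | A count of sessions | Not stated |
| Neurological and safety examinations | Staff | Not stated |

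The safeguard does not reach the first row and probably does not reach the second. It could reach the staff-made rows, but the text does not tie it to any of them.

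**Step 2: how much efficacy evidence rests on instruments.** Nerve conduction is planned in 1 to 2 of every 10 patients. Applied to the 90 in section 3.3, that is 90 × 0.1 = 9 to 90 × 0.2 = 18 patients, or 3 to 6 per arm if spread evenly. It cannot corroborate the primary comparison to any useful degree.

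**Step 3: difference in contact.** From sections 3.4.2 and 3.4.3:

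- EA: 3 × 2 + 2 × 3 = 12 sessions
- CMT: 2 × 2 + 1 × 3 = 7 sessions
- Pregabalin alone: none

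**Step 4: coherence of section 3.6.** The two sentences use the same word, investigator, for a role that cannot be blinded and a role that is. Elsewhere, section 3.6 has unblinded sub-investigators handle allocation, and section 3.8.4 has the sub-investigator record adverse reactions and their causal relationship. The article does not say whether these are the same people.

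**Step 5: illustration only.** The documents give no size for expectation or reporting bias. Assume that both add-on arms report d SD better with no true effect. The arm means are then 0, d, d around a grand mean of 2d/3, and the noncentrality of the three-group ANOVA is

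λ = n × (4/9 + 1/9 + 1/9) × d² = (2/3) n d².

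With n = 30 this is 20d². With n = 30 × (1 − 0.20) = 24, after the dropout in section 3.3, it is 16d². Rejection rates at the two-sided 5% level of section 3.9 are:

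| Assumed d | n = 30 per arm | n = 24 per arm |
|---|---|---|
| 0 | 5.0% | 5.0% |
| 0.2 | 11.3% | 9.9% |
| 0.3 | 20.1% | 16.7% |
| 0.5 | 48.9% | 40.0% |

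Blinding someone who does not rate the outcome changes none of these rates, and neither does changing the label.

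**The case against.** The case on the other side has weight, and most of it narrows the point.

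- **The lack of participant blinding is disclosed.** Open-label stands beside assessor-blinded, section 3.6 says participants cannot be blinded and why, and section 3.8.1 says who fills in the form. A reader might infer that the plan conceals this; it does not. What stands is that section 3.6 offers evaluator blinding as the replacement safeguard without saying that it misses the primary outcome.
- **The label may be true of a role.** A reader might infer that nothing in the trial is blinded. The documents do not support that: nerve conduction, neurological tests and safety examinations are made by staff, and safety is a joint aim. Deleting the label altogether would go too far.
- **The conflict in section 3.6 may come from condensation.** A natural reading is that the treating investigator is unblinded and the evaluating one blinded, and the full protocol may say so. But the article as written states both things of one role, so it needs correcting there.
- **The trial asks an add-on question.** Section 2 compares combined treatment with pregabalin alone, so a real benefit of contact belongs to that contrast and is not plainly a false positive. This stands. Pure reporting bias remains a problem.
- **Some protection exists.** A blinded person handing out forms could limit prompting, and the statistician is blinded. Both are true, but neither reaches the patient's own rating.
- **Questionnaire timing is site procedure.** It is fair that an article may leave this out, so its absence is not counted as a fault. It is proposed only because it is one of the few protections still available.

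**Conclusion.** The point holds in limited form. Assessor blinding does not protect the primary comparison against participant expectation or reporting bias, because the unblinded participant is the assessor. The same applies to the secondary outcomes if the EORTC forms are patient-completed, which is likely but inferred. Section 3.6 also contradicts itself on whether the investigator is blinded.

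The size of any resulting bias cannot be taken from the documents. A reader might take the 11%, 20% and 49% in the illustration as this trial's true error rates. They are not: the shifts of 0.2 to 0.5 SD are assumptions, the rates would apply to any unblinded add-on trial of this size with a patient-reported outcome, and part of such a shift could be genuine benefit from contact.

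The matter should be corrected, because it governs what the trial may claim. It does not invalidate the design, and participant blinding is not being asked for.

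**What to change.** 1. Keep the assessor-blinded term only for the staff-made measurements it covers, for example nerve conduction and neurological or safety examinations. Qualify it accordingly where it appears in the title, abstract and section 3.2.
2. State in sections 3.8.1 and 3.8.2 that FACT/GOG-Ntx is an unblinded patient-reported outcome, and say the same of QLQ-CIPN20 and QLQ-C30 if patients complete them.
3. Rewrite the two sentences in section 3.6 to name which role is blinded and for which measurements, and say whether that role is separate from the unblinded sub-investigators.
4. Have the questionnaires completed before that day's session and away from the treating practitioner.
5. Word the efficacy conclusion as the effect of adding a course of EA or CMT to pregabalin, including contact and expectation, and do not present it as an assessor-blinded finding.

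The cost is a few sentences, one instruction to site staff and a slightly less favourable design claim. Sample size, visits and analysis are unchanged. Step 4 can reduce prompting but does not remove the patient's own expectation, so step 5 is needed in any case.

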#### Secondary outcome

3.8.2

Secondary outcome assessment measures the change and rate of change in the Quality of Life Questionnaire-CIPN 20-Item Scale (EORTC QLQ-CIPN 20) and Quality of Life questionnaire (EORTC QLQ-C30, version 3.0) developed by the European Organisation for Research and Treatment of Cancer in comparison to the baseline.^[22–24]^ EORTC QLQ-CIPN 20 consists of 20 questions, with 9 sensory nerve-related questions, 8 motor neuron-related questions, and 3 autonomic nerve-related questions. A higher score indicates a more severe degree of peripheral neuropathy.^[22]^ EORTC QLQ-C30 is a tool for measuring health-related quality of life and consists of 2 items of the overall functional state, 15 items of function, and 13 items of symptoms. A lower overall score indicates a better quality of life.^[25]^

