### Sample size calculation

3.3

This study is a pilot clinical trial, which aims to evaluate the efficacy and safety of combined treatment with EA and CMT, compared to the conventional-therapy group (pregabalin treatment group). We determined that it would be desirable to proceed with the minimum number of participants possible, to meet the goals of this study. Moreover, earlier clinical studies involving acupuncture or EA for CIPN have included sample sizes of about 20 participants per group.^[17,18]^ Thus, we concluded that this study should include 30 participants in each group (total sample size: 90). Even if the dropout rate is assumed to be 20%, this sample size is larger than that for similar earlier studies.

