### Recruitment, randomization, blinding and non-blinding

3.6

Advertisements for patient recruitment will be posted on the Catholic Kwandong University International St. Mary's Hospital bulletin boards, along with posters, banner advertisements and internet cafes. All advertisements will be run after IRB approval.

Individuals who have given written consent for participating in the study will be assigned a screening number, in order of the outpatient visit at screening. Unblinded sub-investigators, who do not influence the research results and analysis, will refer to the randomization list that has been prepared by a commissioned professional statistician, and assign participation numbers by stratification (based on the presence of breast cancer or colorectal cancer). The randomized list will be generated by layer considering the stratification factor by the block randomization method, and participants will be allocated to the pregabalin group, the pregabalin + EA group, and the pregabalin + CMT group in a ratio of 1: 1: 1. A randomization table is generated by an independent statistician and patients are assigned to one of three groups according to the randomization table. Screening numbers, randomization numbers, and initials assigned to each participant are used as subject identification codes to identify the participant until the end of the clinical trial.

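### If the secondary "rate of change" is a percentage of baseline, it is unstable at low baselines and loses power under ANOVA; baseline-adjusted ANCOVA is a better basis for inference (minor point)

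*Protocol article*

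**What the plan says.** Section 3.8.2 (Secondary outcome) of the protocol article names two forms for each secondary scale: "Secondary outcome assessment measures the change and rate of change", for QLQ-CIPN20 and QLQ-C30, both relative to baseline. It defines neither the second form nor the scoring range of either instrument.

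Section 3.9 (Statistical analysis) fixes the method: "For secondary outcome evaluation, continuous variables are analyzed with ANOVA analysis or Kruskal–Wallis test". No baseline covariate or stratum is included, although section 3.6 stratifies randomisation by cancer type.

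The primary outcome is treated differently, using change only: "Primary outcome assessments are performed with ANOVA analysis to test the differences between the groups for changes in FACT/GOG-NTX at the end of week 5".

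Section 3.3 (Sample size calculation) calls the trial a pilot, plans 30 per group and gives no power target. On attrition it says: "Even if the dropout rate is assumed to be 20%, this sample size is larger than that for similar earlier studies".

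Section 3.5.1 requires CTCAE grade 2 or higher neuropathy at entry but sets no minimum score on either questionnaire.

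**The concern.** A percentage change divides by the patient's own baseline. With a baseline of zero it does not exist, so the patient leaves that analysis because of a baseline value. With a small baseline, an ordinary movement in points becomes a very large percentage, and a few such patients can dominate a group mean and inflate its variance.

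Entry at grade 2 or higher makes a near-zero overall neuropathy score less likely. It sets no floor for the motor and autonomic parts of QLQ-CIPN20 in a patient who qualifies on sensory symptoms, nor for QLQ-C30 symptom items.

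At stake are the precision and readability of the secondary results in a trial with small arms. Separately, analysing change without adjustment leaves unused the baseline score and the stratum, both of which the trial already holds.

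**Working it through.** **Inputs from the protocol article.** Three arms at 1:1:1, 30 per arm, total 3 × 30 = 90. With 20% dropout, 30 × 0.8 = 24 per arm, or 72 patients. Tests are two-sided at 5%. The article states no power, effect or SD for the secondary scales, so there is no planned figure to reproduce.

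**Assumptions.** Score with 28 levels (step 100/27 = 3.7) on 0–100; baseline mean 20–60; SD 15–18; baseline-to-final correlation ρ of 0.5–0.7. Both active arms are lower by 12 points (8 at baseline mean 20), or by the matching proportion. There were 3,000–4,000 simulated trials per setting. Power is that of the overall three-group test.

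**Step 1: why low baselines matter.** Percentage change = 100 × (final − baseline)/baseline. Take a rise of three steps (11.1 points):
- from 3.7 it is 100 × 11.1/3.7 = +300%;
- from 59.3 (16 steps) it is 100 × 11.1/59.3 = about +19%.

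**Step 2: undefined values and spread.** The share of patients with a zero baseline was under 0.1% at baseline mean 60, 1.7% at 40, 5.9% at 30 and 11.3% at 20. Of 72 patients that is about 0.017 × 72 = 1.2, 0.059 × 72 = 4.2 and 0.113 × 72 = 8.1 at means 40, 30 and 20. The SD of percentage change was about 22–29% at mean 60 and about 69–98% at mean 20.

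**Step 3: power, 0–100 scoring, ρ = 0.5.** Each cell gives additive effect / proportional effect.

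| Baseline mean (SD) | ANOVA, percentage | ANOVA, change | ANCOVA on final score |
|---|---|---|---|
| 60 (15) | 0.77 / 0.77 | 0.80 / 0.84 | 0.90 / 0.95 |
| 40 (18) | 0.43 / 0.40 | 0.62 / 0.70 | 0.75 / 0.90 |
| 30 (18) | 0.43 / 0.46 | 0.60 / 0.75 | 0.75 / 0.94 |
| 20 (15) | 0.29 / 0.38 | 0.40 / 0.58 | 0.55 / 0.84 |

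Over all settings run (ρ 0.5–0.7), ANOVA on percentage change lost 1–7 percentage points of power against ANOVA on change at mean 60, 14–31 at means 30–40 and 11–24 at mean 20.

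**Step 4: the same comparison with the other permitted test and with other scoring, ρ = 0.6.** Each cell gives percentage / change.

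| Baseline mean, effect | ANOVA, 0–100 | Kruskal–Wallis, 0–100 | ANOVA, raw sum 9–36 |
|---|---|---|---|
| 60, additive | 0.87 / 0.89 | 0.89 / 0.87 | 0.89 / 0.89 |
| 60, proportional | 0.86 / 0.92 | 0.91 / 0.89 | 0.90 / 0.90 |
| 40, additive | 0.56 / 0.73 | 0.74 / 0.69 | 0.73 / 0.72 |
| 40, proportional | 0.49 / 0.80 | 0.73 / 0.75 | 0.75 / 0.80 |
| 20, additive | 0.37 / 0.47 | 0.49 / 0.45 | 0.49 / 0.47 |
| 20, proportional | 0.45 / 0.69 | 0.57 / 0.63 | 0.66 / 0.69 |

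With Kruskal–Wallis on both forms, the percentage ranges from 5 points better to about 5 points worse. With raw sums that cannot reach zero, the ANOVA results differ by at most about 5 points and nothing is undefined.

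**Step 5: a further run.** With the same arm size and scoring and ρ of 0.5–0.6, ANOVA gave 0.34–0.68 for percentage change and 0.46–0.77 for change, and baseline-adjusted ANCOVA gave 0.60–0.84. Kruskal–Wallis gave 0.49–0.75 for percentage change and 0.43–0.74 for change. The tables show that other choices of baseline and effect move these levels; the ordering under ANOVA does not change.

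**Step 6: why ANCOVA gains.** With equal SD σ at both times, Var(change) = 2σ²(1 − ρ), and the ANCOVA residual variance is σ²(1 − ρ²). Their ratio is (1 + ρ)/2, which is 0.75 at ρ = 0.5 and 0.80 at ρ = 0.6. The stratum was not modelled, so its contribution is not quantified.

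**The case against.** The strongest reply is that the article never says percentage change. The second form could mean change per unit time; at a common visit that is change divided by a constant, and it gives the same ANOVA result as change. This stands: percentage is the likely reading, because the measure sits beside change and is set against baseline, but it remains an assumption.

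A reader might infer that percentage change is less powerful in general. The documents do not support that. Section 3.9 permits Kruskal–Wallis, under which the loss largely disappears, and the article does not say whether scores run from zero.

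A reader might also infer that every secondary score will be tested twice, leaving the better-looking result to be chosen. Section 3.8.2 says what is measured. Section 3.9 gives methods for continuous variables as a class and does not state that both forms are tested separately. Which form leads, and what is done with zero baselines, are commonly settled in a statistical analysis plan, which is not shown here; their absence is no finding.

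Finally, absolute change is retained, the primary outcome uses change only, and the pilot has no power target to miss. All this limits the consequence. It does not answer the narrower point that the article fixes unadjusted methods where a more precise one needs no new data.

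**Conclusion.** The point holds conditionally and is minor. If the second form is percentage change and scores can reach or approach zero, it is undefined or unstable for patients with low baselines and loses power under ANOVA. The illustrative ANOVA ranges are 0.34–0.68 for percentage change and 0.46–0.77 for absolute change, with 0.60–0.84 for baseline-adjusted ANCOVA. These rest on assumed 0–100 scoring, 24 per arm, correlation 0.5–0.6 and assumed means, SDs and effects, none of which the article supplies apart from the arm size and dropout rate. At a high baseline mean the loss is small. The gain from baseline adjustment does not depend on how the second form is read: ANCOVA had more power than ANOVA on change in every setting where both were run. The primary outcome is unaffected.

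**What to change.** In sections 3.8.2 and 3.9, base inference for each QLQ-CIPN20 and QLQ-C30 score on ANCOVA with that score's own baseline and the cancer-type stratum as covariates. Define the rate of change, and if it is a percentage keep it descriptive, for example derived from the adjusted means, which avoids dividing by individual baselines.

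The cost is a short edit in two sections and the ethics approval that section 3.10.2 requires for an amendment. No extra data are needed, since baseline scores and cancer type are already collected. The one loss is that per-patient percentage change is no longer tested.

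### The QLQ-C30 is read through one undefined overall score (lower is better), although it is described as three unlike blocks that should be analysed separately, each in its own direction

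*Protocol article*

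**What the plan says.** Section 3.8.2 (Secondary outcome) of the protocol article names two secondary instruments, the QLQ-CIPN20 and the QLQ-C30. Both are assessed as change and rate of change from baseline.

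The QLQ-C30 "consists of 2 items of the overall functional state, 15 items of function, and 13 items of symptoms". The next sentence gives the only reading rule for it: "A lower overall score indicates a better quality of life". The section does not say how an overall score is formed, how the items in each block are coded, or whether any block is reversed before pooling.

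Section 3.9 (Statistical analysis) adds only a test family: "For secondary outcome evaluation, continuous variables are analyzed with ANOVA analysis or Kruskal–Wallis test". It names no QLQ-C30 scale and does not change the reading rule.

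**The concern.** One direction for one total is natural when all items measure the same kind of thing. The other secondary instrument is such a case: "EORTC QLQ-CIPN 20 consists of 20 questions, with 9 sensory nerve-related questions, 8 motor neuron-related questions, and 3 autonomic nerve-related questions". All of its items concern nerve problems, so a single statement that higher is worse fits.

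The QLQ-C30 is described differently. Symptoms are something a patient wants less of, while overall state and function are something a patient wants more of. A single lower-is-better rule fits a symptom block directly. It fits the other two blocks only if their items are coded as problems, which the article does not say.

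Two things are at stake. If the blocks run in different directions, the total can shrink a real improvement or show it with the wrong sign. Whatever the coding, a total cannot show whether function and symptoms moved together or apart. The QLQ-C30 is the only secondary instrument that the article describes as measuring health-related quality of life, so no other secondary result would reveal this.

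**Working it through.** The article gives no QLQ-C30 result or scoring formula to reproduce. The item counts are consistent: 2 + 15 + 13 = 30 for the QLQ-C30, and 9 + 8 + 3 = 20 for the QLQ-CIPN20.

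**Inputs.** The block sizes 2, 15 and 13 and the lower-is-better rule come from section 3.8.2. Three things are assumed because the article does not give them: a 0–100 scale for every item, a true improvement of 10 points on every item, and the coding direction of each block. The codings are therefore shown as a range.

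**Formula.** Improvement counts as −10 in a block coded higher = worse and as +10 in a block coded higher = better.
- Item-weighted change = (sum over blocks of sign × items × 10) / 30
- Equal-block change = (sum over blocks of sign × 10) / 3

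| Assumed coding | Item-weighted change | Equal-block change | Reading under the stated rule |
|---|---|---|---|
| 1. All blocks higher = worse | (−2 − 15 − 13) × 10 / 30 = −10.0 | −10.0 | Better, correct |
| 2. Only overall state higher = better | (2 − 15 − 13) × 10 / 30 = −8.67 | (1 − 1 − 1) × 10 / 3 = −3.33 | Better, but diluted |
| 3. State and function higher = better, symptoms higher = worse | (2 + 15 − 13) × 10 / 30 = +1.33 | (1 + 1 − 1) × 10 / 3 = +3.33 | Slightly worse, wrong |
| 4. All blocks higher = better | (2 + 15 + 13) × 10 / 30 = +10.0 | +10.0 | Worse, wrong |

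The same uniform improvement reads anywhere from −10 to +10, and only coding 1 gives the full effect with the right sign.

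**One block improving alone, coding 3.** Function: 15 × 10 / 30 = +5.0, read as worse. Symptoms: −13 × 10 / 30 = −4.33, read as better.

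**Function worsens while symptoms improve.** Let symptoms improve by 10 points and function worsen by x, with item weights.
- Where function and symptoms are coded the same way (codings 1, 2 and 4), the two cancel when 15x = 13 × 10, so x = 130 / 15 = 8.67. An 8.67-point loss of function then hides a 10-point symptom gain completely.
- Under coding 3 the two do not cancel. Both lower the total: −(13 × 10 + 15 × 8.67) / 30 = −(130 + 130) / 30 = −8.67. The loss of function is counted as benefit.

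The mechanism differs, but under each coding the total can conceal the loss of function.

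**Blocks analysed separately.** The uniform improvement appears as 10 points in each block under any coding, provided that each block's direction is stated.

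**The case against.** The strongest reply is that the sentence is a one-line note on how to read the instrument, in a journal article that condenses a longer protocol. Section 3.8.2 does not say that the overall score is the tested variable, and neither does section 3.9. Which scales are scored, and how, is commonly left to the full protocol or the analysis plan. This stands in part: the absence of scale definitions is not a fault. The point rests on what the article does state, a single score with a single direction, which section 3.9 leaves in place.

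A reader might infer that the stated direction is simply wrong, or that the article itself says higher is better for state and function. The documents do not support either. Section 3.8.2 counts the items per block and gives no coding. If all 30 items run higher = worse, the rule is coherent.

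A reader might also conclude that the between-group QLQ-C30 comparison is uninterpretable. That goes too far, since it would require a total of mixed direction to be what is actually analysed. Tests are two-sided ("All statistical tests will be performed as two-sided tests with a significance level of 5%, and two-sided 95% confidence intervals"), so a mislabelled direction alone changes the verbal conclusion and not the p-value. Mixed coding inside the total is different, because it changes the quantity being tested.

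Finally, any composite allows its parts to offset one another, and that alone is not an error. It matters here because the parts are unlike and the composite is undefined.

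**Conclusion.** The point holds as a correction to a stated reading rule for a secondary outcome. One undefined total with one direction does not suit the three blocks that the article itself lists. Its sign is fully coherent only if every item is coded higher = worse.

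The size depends on coding that the article does not give. For an assumed 10-point improvement on every item, the item-weighted total moves −10.0 in the coherent case and +1.33 if state and function are scored higher = better. A reversed conclusion is therefore possible but not shown. The risk of concealing a loss of function does not depend on which of the four codings applies. With item weights, 8.67 points of lost function can cancel a 10-point symptom gain or, if the two blocks run in opposite directions, be counted as further benefit.

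The consequence is moderate: a secondary outcome in a trial that calls itself a pilot. The change is worth making because it needs no new data.

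**What to change.** Delete the sentence on the overall score. State that overall state, function and symptom scales of the QLQ-C30 are analysed and reported separately, each scored and read in the direction given by the instrument's scoring rules, with that direction written beside each scale. The full protocol and any analysis plan should carry the same wording.

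Which scale leads is the sponsor's choice; nothing in the article requires a particular one.

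The cost is protocol wording, a few more tables and more secondary comparisons. The questionnaire is already collected in full.
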